## Abstract

**Background:**

There is a growing body of literature highlighting the role that wearable and mobile remote measurement technology (RMT) can play in measuring symptoms of major depressive disorder (MDD). Outcomes assessment typically relies on self-report, which can be biased by dysfunctional perceptions and current symptom severity. Predictors of depressive relapse include disrupted sleep, reduced sociability, physical activity, changes in mood, prosody and cognitive function, which are all amenable to measurement via RMT. This study aims to: 1) determine the usability, feasibility and acceptability of RMT; 2) improve and refine clinical outcome measurement using RMT to identify current clinical state; 3) determine whether RMT can provide information predictive of depressive relapse and other critical outcomes.

**Methods:**

RADAR-MDD is a multi-site prospective cohort study, aiming to recruit 600 participants with a history of depressive disorder across three sites: London, Amsterdam and Barcelona. Participants will be asked to wear a wrist-worn activity tracker and download several apps onto their smartphones. These apps will be used to either collect data passively from existing smartphone sensors, or to deliver questionnaires, cognitive tasks, and speech assessments. The wearable device, smartphone sensors and questionnaires will collect data for up to 2-years about participants’ sleep, physical activity, stress, mood, sociability, speech patterns, and cognitive function. The primary outcome of interest is MDD relapse, defined via the Inventory of Depressive Symptomatology- Self-Report questionnaire (IDS-SR) and the World Health Organisation’s self-reported Composite International Diagnostic Interview (CIDI-SF).

**Discussion:**

This study aims to provide insight into the early predictors of major depressive relapse, measured unobtrusively via RMT. If found to be acceptable to patients and other key stakeholders and able to provide clinically useful information predictive of future deterioration, RMT has potential to change the way in which depression and other long-term conditions are measured and managed.

**Electronic supplementary material:**

The online version of this article (10.1186/s12888-019-2049-z) contains supplementary material, which is available to authorized users.

## Background

The last decade has seen an explosion in the capability of monitoring individuals via sensors in smartphones or wearable devices, and the range of parameters which can be measured by such technologies will continue to grow [1]. The development of remote measurement technologies (RMT), using these inbuilt sensors to unobtrusively measure human behaviour and physiology, combined with active measurement of daily experiences via smartphone apps, is an innovation which could be used to provide real-time information about patients’ current clinical state, as well as information potentially predictive of future deterioration [1].

Major Depressive Disorder (MDD) is associated with a wide range of negative outcomes including: premature mortality [2]; reduced quality-of-life [3]; loss of occupational function [4]; and is often experienced alongside physical comorbidity [5] and approximately 55% will go on to develop chronic depression, characterised by periods of recovery and relapse [6, 7]. Developing interventions which can disrupt the pattern of remission and relapse is of crucial importance to maintain sustained periods of recovery [8]. Predictors of depressive relapse include disrupted sleep [9], reduced sociability [10], changes in mood [11], prosody [12] and cognition [13], and there is evidence highlighting the impact psychological and pharmacological interventions can have on reducing risk of relapse [14, 15]. Identifying the optimal time to deliver a preventative intervention, when these symptoms may be sub-threshold, context dependent, or too subtle for the individual to recognise, is challenging. Symptom recall in patients with depression may also not be accurate, potentially biased by current symptom severity and environmental stressors [16, 17]. This retrospective recall cannot capture symptom variability and context reactivity which would allow interventions to be administered at a crucial point in the relapse signature.

RMT may provide a solution to these problems by giving richer, objective characterisation of behaviour, cognition, speech and physiology. Data can be collected with excellent temporal resolution, including an ability to assess diurnal variation which may be indicative of early decline in mood [18]. Passive RMT (pRMT) uses sensors in activity monitors and smartphones to gather data with no input from the wearer [19], including Global Positioning System (GPS), accelerometer, gyroscope, communication logs, ambient noise and light levels and screen interactions. Many of these sensors have been used to identify changes in sleep, communication and activity patterns associated with depressive episodes [20, 21]. Prosodic speech characteristics, such as speaking rate, pitch, pause duration and energy, collected via smartphone microphones, have been used to detect depression with a prediction accuracy of 81.3% [22]. Active RMT (aRMT) uses smartphone apps to deliver validated questionnaires, cognitive games, speech tasks or electronic diaries using the experience sampling method (ESM) to provide fine-grained understanding of mood changes and stressors in the context of daily life [23]. aRMT has been used to measure affect, cognitions, thoughts, mood and behaviours in real-time, with evidence highlighting the increased validity of this methodology in comparison to traditional retrospective reports [24]. aRMT assessments of positive and negative affect have also been found to be reliably indicative of mood state [25, 26] and have been associated with MDD symptoms [27].

Despite this growing body of research evidence, there has been limited assessment of the utility of multi-parametric RMT in clinical populations [28, 29], combining multiple sensors to detect signatures potentially useful for predicting outcomes in MDD. This protocol describes the clinical study designed to test this utility of RMT.

### Patient involvement in the RADAR-MDD study protocol

Systematic reviews have identified the barriers and facilitators of RMT uptake [30]; service-user focus groups have identified the outcomes prioritised by service-users, identified appropriate methods of measuring these outcomes, and investigated the use of technology to measure and manage symptoms [31]; surveys and user experience testing have informed the selection of devices and development of all user-facing systems to ensure optimal usability and functionality. Extensive device-selection procedures combined all acquired knowledge from literature reviews, focus groups and scoping exercises to provide a short-list of suitable activity monitors. Participant-facing documents (such as information sheets and consent forms) were developed in collaboration with service-user research groups to ensure materials are understandable and describe the technology and protocol in clear language.

### Study objectives

RADAR-MDD is a clinical study aiming to assess the utility of multi-parametric RMT in clinical populations with MDD.

Specifically, RADAR-MDD aims to:Determine the usability, feasibility and acceptability of, and adherence to, RMT to provide real-time objective multidimensional indications of clinical state in individuals with MDD.Improve and refine clinical outcome measurement using RMT as a means of identifying current clinical state.Determine whether multi-parametric RMT collected in populations with recurrent MDD can provide information predictive of depressive relapse and other critical outcomes including anxiety, quality-of-life, and MDD remission.

## Methods

### Study design

RADAR-MDD is a multi-centre prospective observational cohort study in which 600 individuals with a recent history of MDD will be asked to download several RMT apps and use an activity tracker for up to 2 years of follow-up. The study involves no randomisation or intervention, and uses commercially available activity trackers and smartphone sensors.

### Study population

An estimated 100 relapses are required in order to provide sufficient power on which to test the predictive utility of RMT, if 10 variables were entered into the predictive model [32]. With an approximated annual relapse rate of 33% (a lower estimate than that provided in the Star*D trial; [33]), 300 participants would be required, followed-up for one year. Although there is evidence to suggest promising uptake to RMT protocols, the attrition rate in this length of follow-up is unknown, there are likely to be missing data, data are inherently “noisy”, and the relapse rate in our population may be lower than anticipated. We therefore aim to recruit a total of 600 individuals with a history of MDD across three research sites.

The eligibility criteria for inclusion in this study are summarised in Table 1. To recruit people at risk of relapse during the follow-up period, people with a recent history of MDD, with indication of a recurring trajectory will be approached to participate. No limitations have been applied regarding any treatment they may be receiving, although medication use and other psychological interventions will be monitored throughout the course of follow-up. Additionally, participants will be eligible to participate regardless of whether they are currently experiencing depression symptoms or not.

**Table 1 Tab1:** Eligibility criteria for participation in RADAR-MDD

Inclusion criteria	Exclusion criteria
Meet DSM-5 diagnostic criteria for diagnosis of non-psychotic MDD within the past 2 years. Recurrent MDD (a lifetime history of at least 2 episodes of depression; (LIDAS) [34]). Willing and able to complete self-reported assessments via smartphone. Able to give informed consent for participation. Fluent in English, Spanish, Catalan or Dutch language Existing ownership of Android smartphone or willingness to use an Android smartphone as their only smartphone. Aged 18 or over	Lifetime history of bipolar disorder, schizophrenia, MDD with psychotic features, schizoaffective disorders. Dementia History of moderate to severe drug or alcohol dependence within the last 6 months History of major medical disease which might impact upon the patient’s ability to participate in normal daily activities for more than 2 weeks (e.g. due to likely hospitalisations or other periods of indisposition). Pregnancy

### Study procedures

Participants will be recruited over eighteen months from three international clinical cohorts or research infrastructures held at King’s College London (UK); the Netherlands Study of Depression and Anxiety and other available patient groups at Vrije Universiteit Medisch Centrum (VUmc; Amsterdam, The Netherlands); and Centro de Investigacion Biomedican en Red (CIBER; Barcelona, Spain). The schedule of observations is available in Table 2. The flow of participants through the study, including reasons for not participating in the study will be standardised across sites and documented in a flowchart (Fig. 1).

**Table 2 Tab2:** Schedule of events for RADAR-MDD

Month	-1	0	1	2	3	4	5	6	7	8	9	10	11	12	…	23	24
Visit	0	1	n/a	n/a	n/a	n/a	n/a	n/a	n/a	n/a	n/a	n/a	n/a	n/a	n/a	n/a	2
Study explanation (T)	X																
Informed consent (F2F)		X															
Introductory training (F2F)		X															
Baseline assessments																	
Socio-demographics (R/F2F)		X															
Social Environment (R/F2F)		X															
Medical History (R/F2F)		X															
Depression History (R/F2F)		X															
Process evaluation																	
Qualitative interview (F2F/T)					X									X			X
TAM (R)					X									X			X
PSSUQ (R)					X									X			X
Remote Data Collection																	
Wearable sensors			Continuous months 1–24														
Smartphone sensors (pRMT)			Continuous months 1–24														
ESM assessment (aRMT)*		X	X	X	X	X	X	X	X	X	XX	X	X	X	X	X	
Speech (aRMT)		XX	XX	XX	XX	XX	XX	XX	XX	XX	XX	XX	XX	XX	XX	XX	XX
Mood, PHQ8 (aRMT)		XX	XX	XX	XX	XX	XX	XX	XX	XX	XX	XX	XX	XX	XX	XX	XX
Self-esteem RSES (aRMT)		XX	XX	XX	XX	XX	XX	XX	XX	XX	XX	XX	XX	XX	XX	XX	XX
Cognition (THINC-IT) *		X	X	X	X	X	X	X	X	X	XX	X	X	X	X	X	
Outcome assessment																	
Relapse IDS-SR/CIDI-SF (R)		X			X			X			X			X			X
Anxiety GAD7 (R)		X			X			X			X			X			X
Quality-of-life WSAS (R)		X			X			X			X			X			X
BIPQ (R)		X			X			X			X			X			X
Remission IDS-SD/CIDI-SF (R)		X			X			X			X			X			X
CSRI (R)		X			X			X			X			X			X
LTE-SR (R)		X			X			X			X			X			X
Treatment information (R)		X			X			X			X			X			X
Alcohol use AUDIT (R)		X			X			X			X			X			X
Clinical Interview (F2F/T)		(X)			(X)			(X)			(X)			(X)			(X)

T: Telephone. F2F: face-to-face. R: REDCap web-based platform. pRMT: passive remote measurement app. aRMT: active remote measurement app. (X): clinical interview only conducted in people identified as MDD relapse cases by IDS-SR/CIDI-SF primary outcome measurement. X delivered once per month. XX delivered twice per month (every 2-weeks). *ESM and cognition tests are conducted once every 6 weeks

**Fig. 1 Fig1:**
[figure not shown]
Participant flowchart

Recruitment procedures will vary slightly across sites. Potentially eligible individuals will be identified either through existing research cohorts (in London and The Netherlands) who have given consent to be contacted for research purposes, or through mental health services (in London and Barcelona). These individuals will be contacted by a member of the on-site research teams and sent the study information sheet and consent from. Those who provide verbal consent to participate will have a more detailed conversation with the research teams, during which they will have an opportunity to ask questions about the study, have their eligibility confirmed, and arrange a suitable time for enrolment.

Enrolment will either happen at the research centre, or at the participant’s home depending on the site they have been recruited from. Participants will receive a £15/€20 for enrolling in the study, and £5/€10 for every three months of continued participation. Participants who take part in additional qualitative interviews at 3-month or 1-year follow-up will receive £10/€10 per interview. Written consent will be obtained, during the enrolment session, which will include collection of sociodemographic, social environment, medical history and technology use questionnaires, and lifetime depression history measured through the Lifetime Depression Assessment – Self-Report (LIDAS [34];), alongside baseline data collection of all outcome measures via Research Electronic Data Capture (REDCap) software [35].

### Remote data collection

RADAR-MDD is the clinical study in depression being undertaken as part of a larger body of work managed by the Remote Assessment of Disease and Relapse – Central Nervous System (RADAR-CNS; [36]) international research consortium. This includes similar clinical studies conducted in epilepsy and multiple sclerosis, as well as teams dedicated to patient and public involvement, integration into care pathways, regulation. Software engineers, data scientists and software developers have developed an open-source platform to support data collection via wearable devices. More detailed technical information about this open-source platform and the sensors available for use is provided elsewhere [37]. Below is a summary of the methods of remote data collection used in the RADAR-MDD study.

#### Passive RMT (pRMT) app

All modern smartphones comprise the sensors required for measurement in RADAR-MDD, however our study will only incorporate Android smartphones. For participants who do not use a smartphone, we will offer to provide a suitable smartphone for them. Participants who are using a non-Android smartphone will not be recruited unless they explicitly state that they are willing to switch to an Android smartphone as their only phone for the duration of follow-up, and in these cases an appropriate phone will be provided. Each participant will be asked to install the purpose-built pRMT application. This will run in the background, requiring minimal input from participants, collecting data on ambient noise, ambient light, GPS location, keystokes (at the London site only), Bluetooth connectivity, length and duration of calls, number of text messages and emails and weather conditions, in addition to battery life. GPS location data will be obfuscated; that is, providing relative location data, not absolute coordinates, preventing identification of an individual’s home address or precise geographical location.

#### Active RMT (aRMT) app

Following extensive focus group work and user testing [31], an additional app has been created to administer the aRMT aspects of the study protocol. This includes validated questionnaires to measure depressive symptoms and self-esteem. Variability of depressive symptoms will be measured via the 8-item Patient Health Questionnaire (PHQ8; [38]) every 2 weeks throughout the course of follow-up. Variation in self-esteem will be measured using the Rosenberg Self-Esteem Scale; RSES [39]. The RSES is a widely-used 10-item self-reported questionnaire used to quantify self-esteem along a continuum and will be administered alongside the PHQ8 every 2 weeks.

As with the PHQ8 and RSES, every 2- weeks participants will be asked to complete a speech task. This requires participants to say aloud, in a quiet area, some excerpts from “The North Wind and the Sun”, which are shown to be phonetically balanced across all three languages [40]. These will be offered on a random schedule to prevent rehearsal and fluency and preserve prosodic features. In addition to this, participants will be asked to respond to the following question: “Can you describe something you are looking forward to this week?”

The aRMT app will also deliver an ESM schedule (see online Additional file 1), which has been designed to collect brief, in-the-moment assessments relating to several of our domains of interest: mood, stress, sociability, activity and sleep. Participants will receive a series of questions intended to reflect their current state (such as “right now, I feel content”), with 7-point Likert scale answer options (0 = Not at all, 7 = Very much). The ESM schedule consists of approximately 44 items, taking up to 3-min to complete, delivered 9 random times per day within 90-min blocks starting from 08.30 and ending at 22.00 for 6 consecutive days every 6 weeks.

Cognitive function will also be measured using the THINC-IT® app, which has been specifically designed and validated to screen for cognitive dysfunction in depression [41], and includes assessments of elements of executive function such as memory, concentration, and attention.

#### Wearable sensors

The wearable device planned for use in RADAR-MDD is the FitBit Charge 2. Participants will be asked to wear this device for the duration of follow-up, providing ongoing data collection of accelerometery and heart rate, which provide information about movement, daytime activity, sedentary activity, physical exercise, step count, sleep efficiency, sleep latency, wake episodes, sleep fragmentation and post-midnight sleep start. The FitBit Charge 2 was selected due to its commercial availability, its competitive pricing, and the range of measurements available. Furthermore, it met several usability requirements highlighted by our focus groups and patient advisory boards, including: additional utility of a watch-face; comfort and durability; provided by a well-known brand (therefore reducing any potential stigma or identification as “research participant”); an acceptable battery life (3–5 days, requiring approximately 30 min to charge fully), and an excellent app interface. In research environments, the FitBit has also been found to be acceptable for use by depressed samples across a relatively long period of follow-up [42], and has recently demonstrated good ability to accurately identify sleep-wake state and sleep stage cycles [43].

### Outcome measurements

Measurements will be taken at baseline, then every three months for the duration of follow-up (up to 2 years). All outcomes will be collected via Research Electronic Data Capture (REDCap) software [35], which sends automatic survey invitations and reminders to participants for the duration of the study.

#### Primary outcome

##### Major depressive disorder relapse

The presence of MDD during follow-up will be defined as meeting criteria for MDD according to the Wold Health Organisation’s Composite International Diagnostic Interview – Short Form (CIDI-SF; [44]). The CIDI-SF has been used extensively on web-based platforms, and has shown excellent sensitivity and specificity to identify current MDD state [44]. Additionally, a score of > 25 on the the Inventory of Depressive Symptomatology – Self-Reported (IDS-SR; [45]) will be required to establish that the severity of the depressive episode is at least moderate. The IDS-SR is a 30-item questionnaire, widely used in depression trials and providing detailed information on depressive symptoms, including all 9 Diagnostic and Statistical Manual (DSM) domains, symptoms commonly associated with depression (such as irritability or pain), melancholic symptoms and atypical symptoms. Scores on each of the 30 items are summed to create a total score ranging from 0 to 84, with the following thresholds: 0–13 (no symptoms); 14–25 (mild symptoms); 26–38 (moderate symptoms); 39–48 (severe symptoms); 49–84 (very severe symptoms) [45]. In the case of IDS-SR/CIDI-SF identified relapse, a confirmatory diagnostic interview will be conducted, to additionally confirm of relapse onset.

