#### Secondary outcomes

*Anxiety* will be measured via the 7-item Generalised Anxiety Disorder questionnaire; GAD7 [46], which provides a dimensional score of anxiety symptoms which are frequently comorbid with depression. *Quality-of-life/disability* will be measured via the Work and Social Adjustment Scale; WSAS [47], which is a 5-item assessment of perceived social and work-related functional impairment used widely across a range of mental and physical disorders. *Illness perceptions* will be assessed using the Brief Illness Perceptions Questionnaire; BIPQ [48]. The BIPQ provides an insight into the participant’s views about their underlying condition – including a measure of how well they see themselves coping with its symptoms and treatments. *Alcohol use* will be measured using the self-reported Alcohol Use Disorders Identification Test (AUDIT), which has been found to be a reliable and valid method of identifying at-risk and alcohol-dependent drinkers [49]. *MDD remission*, the confirmation of continued remission status, or new remission status in participants who had previously relapsed, will be established using the IDS-SR followed by CIDI-SF. Participants scoring < 14 on the IDS-SR and who do not meet CIDI-SF criteria for MDD will be considered in a state of remission.

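### The relapse outcome is defined as being in MDD at follow-up, with no requirement of prior non-MDD status, although people already depressed may enrol, so episodes persisting from baseline are scored as relapses

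*Protocol article*

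**What the plan says.** All places are in the protocol article.

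- **Outcome rule** (Primary outcome, Major depressive disorder relapse). The diagnostic part reads "The presence of MDD during follow-up will be defined as meeting criteria for MDD according to" the CIDI-SF. The severity part follows: "Additionally, a score of > 25 on the the Inventory of Depressive Symptomatology". The same section says of the CIDI-SF that it "has shown excellent sensitivity and specificity to identify current MDD state". No earlier remission, symptom-free interval or change from the preceding assessment is required.
- **Interview** (same section). "In the case of IDS-SR/CIDI-SF identified relapse, a confirmatory diagnostic interview will be conducted, to additionally confirm of relapse onset".
- **Abstract, Methods.** "The primary outcome of interest is MDD relapse, defined via the Inventory of Depressive Symptomatology- Self-Report questionnaire (IDS-SR"; the sentence then adds the CIDI-SF and nothing else.
- **Table 2 and its footnote.** The relapse measure is scheduled at month 0 as well as at follow-up. So is the clinical interview, which the footnote restricts to relapse cases identified by the two questionnaires.
- **Eligibility** (Study population). "participants will be eligible to participate regardless of whether they are currently experiencing depression symptoms or not".
- **Remission** (Secondary outcomes). "Participants scoring < 14 on the IDS-SR and who do not meet CIDI-SF criteria for MDD will be considered in a state of remission". This state is a secondary outcome and is not made a condition for relapse.
- **Analysis** (Statistical and analysis plan). The predictive model takes relapse as a yes/no outcome and is judged mainly on sensitivity and specificity. No at-risk set is stated.

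**The concern.** Relapse is a transition: a person who was out of an episode enters one. The rule records only whether the person is in an episode of at least moderate severity when assessed. In a cohort restricted to people in remission at entry the two would largely coincide at the first follow-up. Here they need not, because entry does not depend on current symptoms. Someone positive at baseline and still positive at month 3 satisfies every stated condition without having relapsed.

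The study objectives separate identification of current clinical state (the second aim) from prediction of relapse (the third). Scoring persistence as relapse merges them. For a persistent case, the features aggregated before the assessment were collected during the very episode being predicted. Sensitivity and specificity would then describe a mixture of recognising ongoing illness and anticipating new illness, and could not be read as accuracy for relapse.

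**Working it through.** **1. Can the text exclude a persistent case?** Take a participant who meets both criteria at baseline and at month 3.

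- Eligibility: admitted.
- Outcome rule: CIDI-SF met and IDS-SR above 25, so positive. Persistent episodes with IDS-SR of 25 or less are not counted.
- Prior status: not part of the rule.
- Interview: takes place after the questionnaires have identified a relapse. Nothing says that an onset before enrolment, or an onset that is not confirmed, reverses the classification.
- Table 2: a positive relapse measure at month 0 can only reflect an existing state, yet the footnote's label for such a person is a relapse case.

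Followed as written, the participant is scored as relapsed.

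**2. The plan's own figure.** Study population gives 100 relapses needed, 10 variables, a 33% annual relapse rate, and 300 participants followed for one year.

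- Events per variable: 100 / 10 = 10.
- Participants: 100 / 0.33 = 303, stated as 300.
- Reverse check: 300 × 0.33 = 99 relapses.

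The figure reproduces, but it applies the 33% to everyone enrolled.

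**3. Share of scored relapsers who are persistent cases, over one year.** Two inputs are not in the documents and are assumed: f, the share positive at entry (10-50%), and s, the share of those still positive at a follow-up assessment (30-70%). Those positive at entry are treated as not at risk of a new episode in year 1.

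- Persistent = 300 × f × s
- New onset = 300 × (1 − f) × 0.33
- Share = persistent / (persistent + new onset)

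| f | s | Persistent | New onset | Share |
|---|---|---|---|---|
| 10% | 30% | 9 | 89.1 | 9% |
| 30% | 50% | 45 | 69.3 | 39% |
| 50% | 70% | 105 | 49.5 | 68% |

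The share does not depend on the number enrolled.

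**4. Expected new-onset relapses in year 1, before attrition.**

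| f | In 300 | In 600 | Enrolled for 100 relapses: 100 / (0.33 × (1 − f)) |
|---|---|---|---|
| 0% | 99 | 198 | 304 |
| 30% | 69 | 139 | 433 |
| 50% | 50 | 99 | 607 |

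Relapses after a later remission, and those in the second year, would add to these counts.

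**The case against.** **The interview establishes onset.** The strongest reply is that the quoted sentence defines presence of MDD, and the interview then supplies the onset. Follow-up procedure and data monitoring speaks of an interview when a relapse is suspected, which can be read as questionnaires raising the suspicion and the interview settling it. This stands as a possible intention, and the interview may remove some persistent cases in practice. It does not settle the matter: the abstract and the Table 2 footnote identify relapse by the questionnaires alone, and no rule lets the interview result change the classification.

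**A condensed article leaves coding of the risk set to fuller documents.** That is fair for details, and the baseline data would allow the separation at analysis. But the article does state a primary outcome rule, and that rule does not fit its own eligibility criteria.

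**Stronger readings that the documents do not support.**

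- *Persistent cases dominate.* At month 3 alone, the central assumptions give 600 × 0.3 × 0.5 = 90 persistent cases. At a quarterly risk of 1 − 0.67^(1/4) = 9.5%, there are 600 × 0.7 × 0.095 = 40 incident cases, so 69% are persistent. New cases have then had only one quarter to accrue. With the same inputs the share is 39% over one year. Over two years, if the rate holds, it is 90 / (90 + 600 × 0.7 × (1 − 0.67²)) = 90 / (90 + 231) = 28%.
- *Accuracy is inflated by a known amount.* Inflation is plausible, but no size can be computed from the documents.
- *The study is underpowered.* In the central case 600 enrolled still give about 139 relapses before attrition, and the target was doubled partly in case the relapse rate proved lower than expected.
- *Remission cannot be recorded for people depressed at entry.* The introductory phrase, "the confirmation of continued remission status, or new remission status in participants who had previously relapsed", leaves them out, but the operative sentence applies to any participant. This is a wording correction.
- *Change features rest on an ill baseline.* The analysis section also allows change from previous time points, so this does not follow.

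**Conclusion.** The point holds. As written, the primary outcome counts moderate or worse MDD present at follow-up, whether new or continuing, in a cohort that may include people already depressed. Reported sensitivity and specificity would then not refer to relapse. This conclusion rests on the text alone and needs no assumed figure.

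The size does depend on assumptions, since neither the share depressed at entry nor the persistence rate is given. Over one year, persistent cases would be about 39% of scored relapsers in the central case and 9-68% across the range. The planning effect is secondary: with 30% not at risk, 300 enrolled give about 69 relapses in year 1 instead of 99. The target of 600 still exceeds 100 events in that case and reaches 99 at 50% depressed at entry, before attrition and within one year of a follow-up lasting up to two. Because the flaw decides what the primary outcome measures, it should be corrected before analysis.

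**What to change.** 1. Count a relapse only when the CIDI-SF and IDS-SR criteria are met after an assessment at which they were not met.
2. Add a sensitivity analysis that requires the protocol's own remission state beforehand (IDS-SR below 14 and CIDI-SF negative). It guards against counting a small dip and return, such as IDS-SR scores of 26, 25 and 26 in someone who stays CIDI-SF positive.
3. Let participants positive at baseline enter the relapse risk set only after their first non-MDD assessment.
4. State whether the interview's finding on onset can overturn a relapse identified by questionnaire, and bring the abstract and the Table 2 footnote into line.
5. Restate the expected number of relapses for the at-risk group, using the observed share positive at baseline.
6. Reword the introductory phrase on remission so that it covers participants depressed at entry.

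The baseline and three-monthly measures are already collected, so the change is to wording and coding. The price is fewer counted events and probably lower apparent accuracy.
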